### Current study

In the present study we aim to evaluate the (cost-) effectiveness of online CCBT for mild to moderate depression in primary care. In a randomised trial we will compare (a) CCBT with (b) treatment as usual (TAU) by a GP, and (c) CCBT in combination with TAU. In a recent Dutch study of Spek et al. (2007), the same CCBT program has shown to be equally effective as group CBT in people over 50 years old with subthreshold depression [28]. Based on the results from a recent systematic review [23] we hypothesise that CCBT will be more effective than TAU by a GP. Furthermore, we hypothesise that CCBT in combination with TAU will be more effective than CCBT alone by increasing treatment adherence. Although some studies have shown that for mild depression a combination of pharmacotherapy and psychotherapy does not appear more effective than psychotherapy alone [29], other studies suggested that patients receiving combined treatments were more likely to stay in treatment and comply to the treatment protocol [30].

Regarding the economic evaluation we hypothesise the following. The self-help intervention CCBT alone implies costs of time spent by the patient on the treatment and costs of the development of the program, while the TAU treatment requires costs related to a GP consult and/or medication. We hypothesise that from a societal perspective, these costs of the intervention CCBT are comparable to the costs of the intervention TAU. However, as a consequence of our hypothesis that CCBT is more effective than TAU, we expect that CCBT will be more preventive in health care use and productivity loss during the follow-up period, and thus result in lower costs compared with TAU by a GP. As a consequence of the expected increase of effectiveness (in terms of depression and quality of life) and decrease of costs, we hypothesise that CCBT is more cost-effective than TAU by a GP. Hypotheses about the intervention CCBT in combination with TAU are that it is both more costly and more effective compared with stand alone CCBT or TAU.

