## Methods

### Design

We will conduct a randomised controlled trial. Patients will be randomly allocated to one of the three following conditions: (a) CCBT, (b) TAU by a GP, and (c) a combination of CCBT and TAU by a GP. The design of the study and the anticipated flow of the participants are graphically shown in Figure 1. The Medical and Ethical Committee of Maastricht University approved the study protocol. The study is registered at the Netherlands Trial Register, part of the Dutch Cochrane Centre (ISRCTN47481236).

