#### Economic evaluation

Since the follow-up period lasts one year and no extrapolation over time will be executed, discounting of costs is not necessary. All costs will be indexed to the year 2007 by means of the price indexes of the Dutch Central Bureau of Statistics (CBS).

For each patient, volumes of care, travels, lost time for receiving care and lost productivity hours will be multiplied by the prices determined for each cost item. Based on the costs per item, costs during the follow-up period will be calculated as the cumulative costs per patient. The costs at baseline and during the follow-up period of the three groups will be compared by the non-parametric bootstrapping method with confidence intervals in percentiles. By bootstrapping, samples of the same size as the original data are drawn with replacement from the observed data [76]. The quality of life and clinical outcome variables will be compared between the three groups at baseline and during the follow-up period using ANOVA.

In case of baseline differences of costs, effectiveness, or utility scores between the patient groups, corrections will be performed [77-79]. The economic evaluation will consist of a base-case cost-effectiveness and cost-utility analysis, and sensitivity analyses. Uncertainty of parameter estimates of the base-cases will be dealt with by these sensitivity analyses [52]. In the base-cases, data will be analysed according to the intention-to-treat principle. Incremental cost-effectiveness ratios (ICERs) will be determined on the basis of incremental costs and incremental effects [52] of (a) stand alone CCBT compared with (b) usual GP care, or (c) a combination of CCBT and usual GP care. The primary outcome measure for the cost-effectiveness analysis is depression measured by the BDI-II, and for the cost-utility analysis the QALY based on the EQ-5D. The cost-effectiveness ratio will be stated in terms of costs per point improvement on the BDI-II, the cost-utility ratio will focus on the net cost per QALY gained. In our primary analysis QALYs will be derived from the EQ-5D using the UK-tariff. Scores on the quality of life domains derived from the WHOQOL-BREF and the sixth domain of the EQ-5D+C will be used to provide in-depth insight into the quality-of-life.

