Non-parametric bootstrap re-sampling techniques will be used to explore uncertainty around estimates of cost-effectiveness derived from the study sample [76]. Decision uncertainty will be represented graphically by means of a cost-effectiveness acceptability curve (CEAC) [52,80,81]. In addition, the net monetary benefit (NMB) will be used to present the cost-effectiveness and cost-utility results in monetary units. The NMB expresses the difference in effects between the intervention groups in monetary values using the threshold willingness-to-pay for a unit of effect, minus the difference in costs between the interventions [52,82]. Since the value that society would place on a unit reduction in BDI-II depression score is unknown, different values will be assumed to calculate the NMB [27]. Regarding the QALY, the Dutch Council of Public Health and Care suggested in 2006 a ceiling of £80.000 per QALY per year [83]. Alternative values, ranging to £80.000 per QALY, will be used to estimate the NMB.

The alternative threshold values of the NMB will be analysed in sensitivity analyses. Other aspects that can be part of a sensitivity analysis are: varying the utility outcome measure by using the SF-6D or alternative tariffs to value the EQ-5D utility (Dutch tariff instead of the UK tariff), or including other effectiveness measures used in the clinical evaluation. Cost prices will be varied as minimum and maximum cost price estimates. Next to the intention-to-treat analysis, a per-protocol analysis can be performed.

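### No cost-effectiveness ratio is planned for combined treatment against usual GP care, and the two planned ratios can flatter the combination if CCBT alone proves dominated or extendedly dominated

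*Protocol article*

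**What the plan says.** The Design section randomises to three arms: "a) CCBT, (b) TAU by a GP, and (c) a combination of CCBT and TAU by a GP". They are alternatives, so the economic question is which of three to adopt.

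The Economic evaluation section defines the ICERs on the incremental costs and effects of "a) stand alone CCBT compared with (b) usual GP care, or (c) a combination of CCBT and usual GP care". CCBT alone is in both contrasts. The Sample size section powers the same two comparisons, which supports reading the sentence as two contrasts and not as a loose list of arms. No section names an ICER for combined versus TAU.

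The Current study section gives two economic hypotheses. For CCBT alone: "we hypothesise that CCBT is more cost-effective than TAU by a GP", through more effect and lower cost. For the combination: "it is both more costly and more effective compared with stand alone CCBT or TAU".

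Other parts of the economic plan are wider than the ICER sentence. On costs: "The costs at baseline and during the follow-up period of the three groups will be compared by the non-parametric bootstrapping method". On effects: "The quality of life and clinical outcome variables will be compared between the three groups at baseline and during the follow-up period using ANOVA". On net monetary benefit (NMB): "The NMB expresses the difference in effects between the intervention groups in monetary values", with no restriction on which pairs. On uncertainty: "Decision uncertainty will be represented graphically by means of a cost-effectiveness acceptability curve (CEAC"), without saying whether the curve is for a pair of arms or for all three.

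**The concern.** With three mutually exclusive options, an ICER guides a decision only when it compares an option with the next cheaper option still in contention. An option that costs more and yields less than another is dominated. An option is extendedly dominated when its ratio against the next cheaper option exceeds the ratio of the next costlier, more effective option against it. Either kind should leave the comparison before ratios are formed.

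The plan fixes CCBT alone as one side of both ratios before the data show whether it is in contention. If it is not, the combination would be judged against an option nobody should choose, and the ratio that matters, combined versus current GP care, is not among those named. An expectation of higher cost with more effect is also the case in which a ratio is needed to judge value, and for the TAU half of that hypothesis none is planned.

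**Working it through.** The protocol gives no cost, QALY or ICER figure for this trial, so there is no plan figure to reproduce. All costs and QALYs below are assumptions, chosen to show the mechanism.

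**Formulas.** ICER = difference in cost / difference in QALYs. NMB at threshold λ = λ × QALYs − cost. Combined versus CCBT is the same ratio as CCBT versus combined, since both signs change.

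| Assumed example | CCBT minus TAU (cost; QALY) | Combined minus TAU (cost; QALY) | CCBT v TAU (planned) | Combined v CCBT (planned) | Combined v TAU (not planned) |
|---|---|---|---|---|---|
| A: CCBT dominated | +300; −0.01 | +400; +0.04 | dominated | 100/0.05 = 2,000 | 400/0.04 = 10,000 |
| B: CCBT dominated | +300; −0.01 | +600; +0.03 | dominated | 300/0.04 = 7,500 | 600/0.03 = 20,000 |
| C: CCBT extendedly dominated | +900; +0.01 | +1,500; +0.05 | 900/0.01 = 90,000 | 600/0.04 = 15,000 | 1,500/0.05 = 30,000 |
| D: pattern the protocol expects | −300; +0.02 | +400; +0.04 | CCBT dominates | 700/0.02 = 35,000 | 400/0.04 = 10,000 |

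Example A in levels: TAU 3,200 and 0.70 QALY; CCBT 3,500 and 0.69; combined 3,600 and 0.74.

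**Does the planned ratio mislead?**

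- A at λ = 5,000: NMB is 0.70 × 5,000 − 3,200 = 300 for TAU, 0.74 × 5,000 − 3,600 = 100 for combined, and 0.69 × 5,000 − 3,500 = −50 for CCBT. TAU is best, yet 2,000 is below the threshold and favours the combination. The conflict runs from 2,000 to 10,000.
- B: the same conflict from 7,500 to 20,000.
- C at λ = 20,000, relative to TAU: combined 0.05 × 20,000 − 1,500 = −500; CCBT 0.01 × 20,000 − 900 = −700. TAU is best, yet the planned 15,000 favours the combination. The conflict runs from 15,000 to 30,000.
- D: CCBT removes TAU from contention, and the choice between CCBT and combined turns at 35,000. The planned pair gives the right answer at every threshold. Here the combined-versus-TAU ratio of 10,000 would be the misleading one, because TAU is dominated.

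**Is the missing contrast lost?** No. Combined minus TAU equals (CCBT minus TAU) minus (CCBT minus combined), for costs, QALYs and NMB alike. In C at λ = 20,000: −700 − (−200) = −500, as above. The two ratios alone, without their numerators and denominators, do not determine it.

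**Acceptability curve.** Probabilities for pairs do not fix the probability that an option is best of three. In a simulation of 200,000 draws of three independent normal NMBs with equal means, P(CCBT beats TAU) and P(CCBT beats combined) were both about 0.50. P(CCBT best of three) was 0.34 with standard errors of 300 in every arm, and 0.42 with standard errors of 100 (TAU), 600 (CCBT) and 300 (combined).

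**The case against.** A reader might infer that combined versus TAU is never estimated, or that a stated hypothesis goes untested. The document does not support that. The hypothesis concerns a cost difference and an effect difference, and both are compared across all three groups. The NMB is not limited to contrasts with CCBT, and at a given threshold NMB ranks three options without any dominance step.

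A reader might also infer that the acceptability curve is a set of pairwise curves against CCBT. The text does not say so. It leaves the form open, which a condensed article may do.

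Three further objections have weight. The two contrasts match the powered comparisons, so the focus on CCBT alone looks deliberate. Under the protocol's expected pattern the planned ratios are enough (example D). At the ceiling of 80,000 per QALY that the Economic evaluation section names, example A reaches the same decision either way: relative to TAU, combined gains 0.04 × 80,000 − 400 = 2,800 and CCBT loses 0.01 × 80,000 + 300 = 1,100. The planned CCBT-versus-TAU contrast would also show openly that CCBT is dominated.

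All of this limits the point but does not remove it. The ICER contrasts are stated, not left to another document. The plan also uses a range of thresholds up to 80,000, and the conflict zones in A to C lie within it. That CCBT will be cheaper and more effective is a hypothesis under test. The Background reports that the one earlier economic evaluation found CCBT more effective but also more costly than usual GP care, and the Discussion notes that its programme had nurse support at each session, which this one lacks.

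**Conclusion.** The point holds as a limited one. The ICERs are fixed as CCBT versus TAU and CCBT versus combined, and no ICER is planned for combined versus TAU. The components of that contrast are recoverable from the planned analyses, and the planned pair is sufficient if CCBT is cheaper and more effective than TAU.

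If CCBT alone is dominated or extendedly dominated, the combined-versus-CCBT ratio overstates the value of the combination: 2,000 against 10,000 per QALY in example A, 7,500 against 20,000 in B, 15,000 against 30,000 in C. It misleads only for thresholds between each pair of values. These sizes rest wholly on assumed costs and QALYs; the document offers none to replace them. It would go too far to say that the trial's economic conclusion will be wrong, since that depends on how the arms fall out and on the threshold used.

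**What to change.** In the Economic evaluation section, replace the two fixed ICER contrasts with a full incremental analysis: rank the three arms by mean cost, remove dominated and then extendedly dominated arms, and compute ICERs between successive remaining arms. Report combined versus TAU alongside, labelled as a pairwise comparison, since it should not drive the decision if TAU is itself dominated.

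Compute the NMB of each arm in every bootstrap replicate, and state that the acceptability curve shows, at each threshold, the probability that each of the three options has the highest NMB.

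The cost is a change of plan wording and a little more analysis on the same data and the same bootstrap. No extra patients or measurements are needed, and the two contrasts with CCBT alone can still be shown.

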### Collaboration

The current study will be conducted in collaboration with several disciplines. The Trimbos-institute (the Netherlands Institute of Mental Health and Addiction) will be involved in the development and dissemination of CCBT. The Pandora foundation (patient organization) acts as an advisor on the design of the study and the dissemination of the results. Several members of the project group work as clinicians in secondary mental health care institutions and have substantial professional contacts in the field. The

Dutch College of General Practitioners (NHG) has been informed about our plans and supports our initiative. Additional research projects will be conducted in collaboration with the Department of Health, Ethics and Society/Metamedica and the Department of Health Organization, Policy and Economics of the Maastricht University. For instance, these projects will focus on topics like the patient perspective on CCBT and quality of life aspects of depression.

## Discussion

Although in the last two decades research attention for CCBT has grown, research on the effectiveness of CCBT for depression in primary care is still in its infancy, especially CCBT offered via the Internet. More research evaluating such interventions is necessary. Therefore, in the current study we will evaluate the (cost-) effectiveness of an online CCBT self-help program for mild to moderate depression in primary care. We will compare CCBT with treatment as usual by a GP, and with a combination of both treatments.

### Why do we need more research on CCBT in primary care?

There are several reasons why we are conducting this study. First, the only study so far on CCBT in primary care used a program that was delivered on a computer in the general practice [26]. Since the Internet can increase the accessibility of such an intervention, we will offer the CCBT program on the Internet. In the Netherlands, almost all of the general adult population has access to Internet, and this will only increase in the next decade [84]. Second, in the only other study on CCBT in primary care [26], a nurse provided practical support at the start and end of each session. We will study the effectiveness of CCBT as a pure self-help intervention; no support or guidance will be given to the patient. Third, the effects of a combined treatment (i.e. both CCBT and treatment as usual by a GP) still need to be evaluated. We think this might have extra effects in terms of improvement in depressive severity and quality of life. Although the GP is not directly involved in the CCBT program, a combined treatment might also increase adherence to the intervention. Previous studies already showed that minimal therapist contact could increase the adherence to Internet-based interventions [85,86], a result which was recently confirmed in a meta-analysis [87]. Next to that, the GP can monitor the progress of the patient and can pay attention to non-verbal signals of the patient. Finally, only one study so far has conducted an economic evaluation of CCBT [27].

### Methodological considerations

Our study has several strengths. First, we will recruit patients from the general population. Unlike in samples selected in general practices or clinics, no biases will occur due to help seeking behaviour of patients and illness recognition by physicians, which is often a problem in depression [10]. Another strength is that we will make full use of the Internet infrastructure by administering all questionnaires online. This reduces the risk of making mistakes while filling out or scoring the questionnaires.

Several limitations of the present study should also be noted. All our outcomes will be measured online and one may question the equality of computerised questionnaires and paper-and-pen versions. However, there are sufficient indications that computerised and paper-and-pen questionnaires show similar construct validity [88,89]. Furthermore, all the outcomes at follow-up will be measured by self-report and as a result information on actual DSM-III diagnoses of depressive episodes at follow-up will be lacking.

## Conclusion

CCBT is a new treatment format with interesting possibilities. It might offer a solution to the current undertreatment of depression. It is a promising treatment for depression in primary care, but more research needs to be done before it can be disseminated and implemented in the current health care system. The current study contributes to the growing literature on the clinical and cost-effectiveness of online CCBT.
